## Abstract

**Background:**

Late-life depression (LLD) has a poorer prognosis and higher relapse rate than younger adults, with up to one third of patients with LLD showing suboptimal response to antidepressant therapy. LLD has been associated with significant impairment in cognition and daily functioning. Few studies have evaluated the therapeutic effects of high-definition transcranial direct current stimulation (HD-tDCS) on depressive and cognitive symptoms of LLD. The current randomized controlled trial assesses the efficacy of HD-tDCS as an augmentation therapy with antidepressants compared to sham-control in subjects with LLD.

**Methods:**

Fifty-eight patients with LLD will be recruited and randomly assigned to the active HD-tDCS or sham HD-tDCS group. In both groups, patients will receive the active or sham intervention in addition to their pre-existing antidepressant therapy, for 2 weeks with 5 sessions per week, each lasting 30 min. The primary outcome measures will be the change of depressive symptoms, clinical response and the remission rate as measured with the Hamilton Depression Rating scale (HAMD-17) before and after the intervention, and at the 4th and 12th week after the completed intervention. Secondary outcome measures include cognitive symptoms, anxiety symptoms, daily functioning and adverse effects.

**Discussion:**

Older adults with depression are associated with poorer outcomes or unsatisfactory responses to antidepressant therapy, and significant cognitive decline. Therefore, a new effective treatment option is needed. This randomized control trial aims at assessing the efficacy of HD-tDCS on ameliorating the depressive, cognitive and anxiety symptoms, and improving the daily functioning of subjects with LLD.

**Trial registration:**

ClinicalTrials.gov NCT05322863. Registered on 11 April 2022.

**Supplementary Information:**

The online version contains supplementary material available at 10.1186/s13063-022-06855-z.

## Administrative information

Note: the numbers in curly brackets in this protocol refer to the SPIRIT checklist item numbers. The order of the items has been modified to group similar items (see http://www.equator-network.org/reporting-guidelines/spirit-2013-statement-defining-standard-protocol-items-for-clinical-trials/).

## Introduction

### Background and rationale {6a}

#### Late-life depression (LLD) has a great impact on the health system

Most of the developed countries are facing a significant challenge of having a significant proportion of their ageing population suffer from depression in which the burden of LLD will continue to increase. LLD, which refers to adults who are 60 years or older, is associated with a poorer long-term prognosis, a more chronic course, and a higher relapse rate than that in younger adults [1]. The treatment response to medication is unsatisfactory. Fewer than 50% of patients with LLD achieve symptomatic remission [2]. Therefore, a new treatment option that is effective and well tolerated by older adults is desperately needed.

#### Alternative treatment options

Transcranial direct-current stimulation (tDCS) is a non-invasive method of neurostimulation in which a weak, direct electric current (amplitude < 2 mA) is applied through electrodes placed on the scalp. It is portable, relatively inexpensive and easy to use. It is also a relatively safe intervention tool with common adverse effects largely limited to the stimulation site including itchiness, redness, tingling and burning sensation and possible transient headache [3]. There are no severe adverse events recorded in more than 40 previous sham-controlled studies of older adults [3]. It exerts its treatment effect by inducing changes in neuronal activity and by modulating synaptic release probability uptake and sensitivity [4]. tDCS enhances long-term plasticity and alters the rate of neurotransmitter release [4]. Its effects have been reported up to an hour after stimulation, which is essential to achieve a persistent treatment effect [5]. One of the main neurological deficits in depression is the serotonin deficit and hypoactivity of the left dorsolateral prefrontal cortex (DLPFC) [6]. Recent evidence suggested that tDCS and serotonin enhance each other’s function. tDCS increases the release of serotonin mediated by the serotonin transporter [7]. In contrast, continuous enhancement of serotonin by antidepressants strengthens the long-term plasticity–like glutamatergic plasticity induced by tDCS [8]. In addition, tDCS was shown to modulate the activity of DLPFC [9, 10], which could modulate the hypoactive condition of the DLPFC in patients with depression. Furthermore, many patients with LLD display significant impairment in executive function, which is associated with a poor treatment response and prognosis in patients with LLD [11]. tDCS has been shown to improve executive function by stimulating the DLPFC region, which may cause an indirect improvement in depressive symptoms and the treatment response in patients with LLD [10]. Such findings support the theoretical treatment potential of tDCS as mono-therapy or augmentation therapy in patients with LLD.

#### Previous experience of tDCS as an intervention for depression

A growing number of studies have examined tDCS as a treatment intervention for depression. In a recent meta-analysis of six randomized controlled trials (RCTs) with 289 adult patients, tDCS was shown to be significantly superior to sham-control treatment in response, remission and improvement in depression. The left DLPFC was stimulated in most studies. The effect size was comparable with those reported for antidepressant drug treatment and for repetitive transcranial magnetic stimulation [12]. Controversial outcomes were noted in recent studies. The recent double-blind, placebo-controlled study compares the effect of tDCS and antidepressant, escitalopram. The result showed escitalopram was superior to tDCS despite no difference in the rates of response/remission [13]. Another large international RCT in adult patients with depression showed no difference in reducing depressive symptoms between active and sham stimulation in patients with unipolar or bipolar depression [14]. The conflicting results warrant further high-quality RCTs to determine the efficacy of tDCS. In addition, most studies have targeted the adult population. Few trials have been performed in older adults, and no RCT has been done in patients with LLD aged 60 or above. Only a small study investigated the effects of tDCS on executive function in older adults with Parkinson’s disease [15]; improvement in executive function was shown after tDCS was applied over the DLPFC region. It is essential to explore the effectiveness and tolerability of tDCS in older adults with depression.

#### Advantages of a new format of tDCS: HD-tDCS

A main drawback of traditional tDCS is the spatial crudity of its effect. The highest cortical current density may not occur directly under the target electrode [15], which probably alters the effects of tDCS and contributes to the conflicting results of existing tDCS studies. High-definition tDCS (HD-tDCS) was developed to address this problem. HD-tDCS is typically performed with more than two smaller electrodes. The most frequently used montage is the ‘4 × 1 ring set-up’, which uses a centre anode electrode surrounded by four return cathode electrodes. The density of the cortical field and spatial focality can be adjusted by changing the diameter of the ring of electrodes [16]. In addition to enhancing the spatial focality of stimulation, the increased effects of neuroplasticity may also be shown by longer-lasting after-effects, as in a previous study of HD-tDCS [17]. At the same time, the tolerability was found to be similar to that of traditional tDCS [18]. No HD-tDCS study of LLD or depression has yet been performed. Therefore, our team conducted a pilot study to test the effects and tolerability of HD-tDCS on subjects with LLD.

#### Results from our pilot study

An open-label pilot study was conducted by our team in 2018 [19]. 15 older adults aged 60 or above who have depression with residual depressive symptoms received five consecutive daily sessions of 20-min active HD-tDCS interventions weekly for 2 weeks. The results revealed that the HD-tDCS was effective in reducing the depressive severity and the remission rates, with a sustained effect at both the 1-month and 3-month follow-up. Pre-post improvements were seen in the overall cognitive functioning and in verbal fluency, but not in executive functioning. No adverse effects were observed. Nevertheless, this was an open-label study with a small sample size. A double-blinded RCT with an adequate sample size is warranted to confirm the efficacy of HD-tDCS as an augmentation therapy with antidepressants in patients with LLD.

### Objectives {7}

The main objective of this study is to determine the efficacy of a 2-week daily programme (10 sessions) of HD-tDCS to augment antidepressant therapy in subjects with LLD who had residual depressive symptoms despite adequate dosage and duration of antidepressant therapy.

Secondary objectives are to evaluate the HD-tDCS impact on the patients’ cognition (including the global cognitive functions, working memory, executive function and attention), anxiety symptoms, and daily functioning, after the 2-week daily programme (10 sessions) of HD-tDCS. The adverse effects of HD-tDCS and the patient’s tolerability will also be evaluated.

### Trial design {8}

The study described in this protocol is a RCT to evaluate the superiority of an active HD-tDCS programme for patients with LLD compared with the sham HD-tDCS programme. Forty-eight patients with LDD will be randomized (1:1) in the active HD-tDCS group or the sham HD-tDCS group.

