### Sample size {14}

The sample size was estimated using G*Power 3.1, based on the results of a tDCS meta-analysis of adult subjects by Kalu et al. [27]. In this study, active tDCS was found to be more effective than sham tDCS for the reduction of depression severity (Hedges’ g = 0.743). For 80% power and an alpha level of 5%, 48 patients (24 in each group) will be needed to detect group differences. To allow for a 20% drop-out rate, 58 patients (29 in each arm) will be recruited.

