## Assignment of interventions: allocation

### Sequence generation {16a}

Block randomization will be used in this study. Each block will consist of eight participants at a 1:1 ratio between the two groups. In the randomization procedure, each participant will be assigned a special number generated by a computer. These numbers will not be decoded until the intervention group is assigned.

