### Methods for additional analyses (e.g. subgroup analyses) {20b}

Post hoc analyses will also be performed with Bonferroni corrected t-tests to investigate the improvements in all outcome variables in pairwise comparisons across various assessment time points. Statistical significance will be set at a *p* value < 0.05. Intention-to-treat last-observation carried-forward scores will be used for the analyses. All computations will be performed using SPSS for Windows, version 22.0.

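### Trial design {8} gives 48 as the number to randomise where the abstract and {14} give 58; as a minor point, 58 covers about 17% drop-out, not 20%

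*Protocol article*

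**What the plan says.** Three places in the protocol article give the size of the trial.

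- Trial design {8}: "Forty-eight patients with LDD will be randomized (1:1) in the active HD-tDCS group or the sham HD-tDCS group".
- Abstract, Methods: "Fifty-eight patients with LLD will be recruited and randomly assigned to the active HD-tDCS or sham HD-tDCS group".
- Sample size {14}: "For 80% power and an alpha level of 5%, 48 patients (24 in each group) will be needed to detect group differences", followed by "To allow for a 20% drop-out rate, 58 patients (29 in each arm) will be recruited". The effect size is a Hedges' g of 0.743 from a meta-analysis of adult tDCS trials, and the software is G*Power 3.1. The section does not say whether the 5% is one-sided or two-sided.

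Two further statements bear on the consequences. Sequence generation {16a} fixes the blocks: "Each block will consist of eight participants at a 1:1 ratio between the two groups". The section on additional analyses {20b} says how drop-outs enter the analysis: "Intention-to-treat last-observation carried-forward scores will be used for the analyses".

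**The concern.** In {14}, 48 is the number required before any allowance for loss, and 58 is the number after it. Section {8} takes the 48 and calls it the number randomised. No sentence elsewhere reconciles the two figures.

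The number to randomise is a core design parameter, and {8} is where a reader looks for the design. A randomisation list built to {8} would also look complete, because 48 is exactly six blocks of eight. Stopping there would use up the whole drop-out allowance before any patient was lost. A reader of the results could not tell whether the trial had met its target.

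Separately, the sentence in {14} that justifies 58 does not hold on its own numbers: losing 20% of 58 leaves fewer than 48.

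**Working it through.** **Inputs.** From {14}: g = 0.743, power 80%, alpha 5%, 24 per group needed, drop-out 20%, 58 recruited (29 per arm). From {8}: 48 randomised. From the abstract: 58 randomised. Allocation is 1:1 ({8}, {16a}). Two assumptions are mine, because {14} names neither the test nor its sidedness: a two-sample t-test, with both one-sided and two-sided 5% tried.

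**Step 1: reproduce the 48.** With n per arm, the noncentrality is 0.743 × √(n/2) on 2n − 2 degrees of freedom.

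- One-sided 5%: the smallest n reaching 80% is 24 (noncentrality 0.743 × √12 = 2.574, power 81.3%). The total is 48, an exact match.
- Two-sided 5%: the smallest n reaching 80% is 30 (power 80.8%), a total of 60. At 24 per arm, two-sided power is 71.2%.

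So 48 is reproduced on a one-sided 5% basis only.

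**Step 2: reproduce the 58.**

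- 48 × (1 + 0.20) = 57.6, rounded up to 58. This matches.
- To keep 48 after 20% loss: 48/(1 − 0.20) = 60.
- Loss that 58 can absorb: (58 − 48)/58 = 10/58 = 17.2%.
- Completers from 58 after 20% loss: 58 × 0.80 = 46.4, or about 23 per arm.

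**Step 3: follow {8} literally.** 48 × 0.80 = 38.4 completers, or about 19 per arm.

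**Step 4: power at g = 0.743.**

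| Per arm | What it represents | One-sided 5% | Two-sided 5% |
|---|---|---|---|
| 19 | completers, 48 randomised, 20% loss | 72.6% | 60.6% |
| 23 | completers, 58 randomised, 20% loss | 79.8% | 69.3% |
| 24 | the number {14} says is needed | 81.3% | 71.2% |
| 29 | all 58, no loss | 87.5% | 79.4% |

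**Step 5: separate the causes.** Going from 24 to 23 per arm, the effect of the inflation formula, costs 81.3 − 79.8 = 1.5 points one-sided or 71.2 − 69.3 = 1.9 two-sided. Going from 24 to 19, the effect of following {8}, costs 81.3 − 72.6 = 8.7 points one-sided or 71.2 − 60.6 = 10.6 two-sided. Changing from one-sided to two-sided at 24 per arm, with nobody lost, costs 81.3 − 71.2 = 10.1 points.

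**The case against.** **The sample size section already explains both figures.** Section {14} distinguishes 48 needed from 58 recruited, the abstract agrees on 58, and {8} is a single summary sentence. That a team would actually stop at 48 is conjecture. This makes 58 the evident intention, but it does not make {8} correct. Nor can the texts be read as 58 recruited with 48 left to randomise after screening: the abstract randomly assigns the 58, and {14} divides them into arms.

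**Drop-outs are not lost from the analysis.** A reader might infer that only 38 or 46 patients would be analysed. The documents do not support that. Section {20b} plans intention-to-treat with the last observation carried forward, so a drop-out with an earlier score stays in. The 38 and 46 are completers, and the powers at 19 and 23 per arm describe a completers-only comparison that the protocol does not plan. If carried-forward scores were as informative as observed ones, 58 analysed would give 87.5% one-sided or 79.4% two-sided, and 48 would give 81.3% or 71.2%. These are upper figures if carrying forward dilutes the effect. This objection stands against any claim about numbers analysed. It leaves the conflict between 48 and 58 untouched, and {14} itself treats drop-outs as a loss by inflating for them.

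**The inflation slip is very small.** This stands. It amounts to two recruited patients (60 against 58) and 1.5 points on the basis that reproduces 48, where 79.8% is in effect the 80% target. It would not merit a point alone.

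**The two-sided powers could mislead.** A reader might take 69.3% or 60.6% as the cost of drop-out. Much of the gap from 80% is the unstated sidedness, since 48 patients with no loss already have only 71.2% two-sided.

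**Conclusion.** The point holds, with its weight on the contradiction. Section {8} gives the wrong number to randomise; the abstract and {14} both say 58. Following {8} with the protocol's own 20% loss would leave about 38 completers, with completer power of about 73% one-sided or 61% two-sided against a stated 80%.

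The drop-out sentence in {14} is also inaccurate, but only slightly: 58 covers 17.2% loss, and 20% loss leaves about 46 completers, with 79.8% power one-sided or 69.3% two-sided. This does not show that a trial of 58 is materially underpowered on the basis used to plan it.

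The powers rest on g = 0.743, a two-sample t-test, equal arms and completers only. The planned repeated-measures analysis with carried-forward scores would differ.

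**What to change.** - In Trial design {8}, give 58 randomised, 29 per arm, so that it agrees with the abstract and {14}.
- In Sample size {14}, replace the drop-out claim with one that is true of 58: either that it allows for about 17% drop-out, or that 20% drop-out leaves about 46 completers. Give the power at 23 per arm together with the sidedness of the 5% test. Without the sidedness, that power could be either 79.8% or 69.3%.

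The cost is two wording corrections and a drop-out allowance that reads slightly less favourably. Randomising 60 would also satisfy the arithmetic for 20% loss, but it is not needed if the allowance is stated as it is. That 60 (48/0.8, before loss) should not be confused with the 60 evaluable patients that a two-sided 5% test would need.

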## Methods: Participants, interventions and outcomes

### Study setting {9}

This 12-week double-blinded randomized sham-controlled trial will assess the efficacy of HD-tDCS as an augmentation therapy with antidepressants in subjects with LLD subjects who had residual depressive symptoms despite adequate dosage and duration of antidepressant therapy.

### Eligibility criteria {10}

The inclusion criteria are as follows:Sixty years of age or aboveRight-handedness, as determined by the Edinburgh Handedness Inventory (to homogenize neuroanatomical targeting)Chinese ethnicityFulfil the criteria of major depressive disorder (single or recurrent episode) and in partial remission, defined by the 5th Edition of the Diagnostic and Statistical Manual of Mental Disorders (DSM-5)Presence of mild to severe levels of depressive symptoms measured and defined by HAMD-17 scores ≥ 8 and ≤ 52 [20]Suboptimal treatment response with at least one adequate antidepressant trial defined as full or best tolerated doses at least 6 weeksStable dosage of antidepressants or other treatments for depression in recent 4 weeksValid informed written consent

The exclusion criteria are as follows:A DSM-5 diagnosis other than depressive disorders (e.g. bipolar and related disorders, schizophrenia spectrum and other psychotic disorders).A Hong Kong Chinese version of the Montreal Cognitive Assessment (HK-MoCA) score below the second percentile according to the subject’s age and education level (to exclude subjects with existing dementia)Substance use disorderActive suicidal ideation or a suicide attempt within the past monthConcomitant unstable medical conditions or major neurological conditionsSignificant communication impairment

### Who will take informed consent? {26a}

Informed consent is obtained from the patients before starting any trial-specific procedure. All participants are advised that participation in research is entirely voluntary and that they can withdraw their participation at any time. The psychiatrist does the first presentation of the study explaining with an information pamphlet detailing the purpose of the study, target audience, length and procedure of the treatment, possible risk factors, benefits of joining the study, summary of the function and effectiveness found in research related to using HD-tDCS as an augmentation treatment. Patients are given time to ask psychiatrists questions and express potential concerns. Patients will be given contact details of the clinical investigator for further enquires. Patients will also be given at least a month to decide whether to join the treatment post presentation of the study by psychiatrists given old adults with a suboptimal response may require some time to consult with families or to make a decision. The protocol is then explained again in detail by the clinical investigator before the signature of the informed consent by the patients.

### Additional consent provisions for collection and use of participant data and biological specimens {26b}

N/A, no biological specimens were collected in this study.

## Interventions

### Explanation for the choice of comparators {6b}

All eligible participants will be randomized to receive an intervention trial of HD-tDCS, either active intervention (a-HD-tDCS) or sham (s-HD-tDCS) as a control, in addition to their pre-existing antidepressant regimen, for 2 weeks with five sessions per week. A total of ten sessions HD-tDCS will be delivered, with each lasting 30 min.

### Intervention description {11a}

HD-tDCS intervention will be performed by formally trained and experienced investigators with hands-on experience in tDCS, who will not be involved in the data collection and analysis. There will be a demonstration and training session involving all staffs in delivering the treatment before the study. Videotape of the first session of each participant’s intervention would be done and reviewed by PI to ensure the quality. The device can also log down the parameter and energy used during the treatment. The intervention will be performed at either psychiatric outpatient clinics or psychiatric day hospitals, where the principal investigator or co-investigators serve on-site. The clinics and day hospitals are equipped with resuscitation facilities. Full-time nursing and support staff are available to handle medical emergencies.

#### High–definition transcranial direct current stimulation (HD-tDCS) group

The HD-tDCS will be administered by Starstim (Neuroelectrics). All participants will receive the treatment by using the same model of the device. The HD-tDCS device can be portable and controlled wirelessly via computer software developed by the manufacturer. The montages will be a ‘4 × 1 ring set-up’, which is the most commonly used HD-tDCS setting. The centre anode electrode is surrounded by four return cathode electrodes. The anode will be placed over the left DLPFC, which is located at F3 based on the 10/20 electroencephalogram system. The four cathodal electrodes will be placed at FC1, AF3, F7 and FC5 (Additional file 1). Conductive electrode gel will be applied on the scalp at all designated electrode stimulation areas. A cap appropriate for each participants’ head size will be used to ensure that the electrodes are secured in place. Impedance checks will be performed using the Starstim software before each treatment session. A 2-mA stimulation will be delivered for 20 min, with the current gradually increased and decreased over 30 s. The patients will be instructed to relax and remain motionless during the intervention. The administrator will closely monitor the impedance throughout each session and record any side effects experienced by the participants. The participants will be allowed 5 min of rest after the intervention and will be actively asked about any discomfort. Each session will last around 30 min, with a total of 10 sessions (two consecutive weeks of treatment for 5 days per week).

